### Measures

Data will be collected (1) at the beginning of a one-week run-in period (week 0); (2) at week 4; (3) upon completion of the intervention (week 8); and (4) post-program (week 12). FOH, self-management, and A1C will be measured, and RT-CGM recordings will be analyzed to determine within-group and between-group differences (Fig. 3).

**Fig. 3 Fig3:**
[figure not shown]
Spirit figure

#### Baseline and post-intervention measures

*Self-report instruments* will be used to obtain demographic, literacy, and health information and previous history of hypoglycemia and diabetes self-management (see Table 3 for a complete list of measures). The scales chosen have strong psychometric properties and have been validated in diabetes populations. The primary outcome, FOH, will be measured using the Worry Subscale of the Hypoglycemia Fear Scale II. This 18-item, five-point Likert scale measures situation-specific worries about hypoglycemia and provides one overall score for hypoglycemic worry. The scale has strong psychometric properties (Cronbach’s alpha 0.95) [53]. Self-management will be measured with the Diabetes Self-Management Scale (Cronbach’s alpha 0.84) [56]. Convergent and construct validity are demonstrated for both scales [53, 56]. *Glycemic control* will be measured with a fingerstick for A1C using previously published methods (A1C Now®, Chek Diagnostics, Indianapolis, IN, USA) [48].

**Table 3 Tab3:** Measures

Variables	Measure	Frequency
Demographic, health, and literacy information	Demographic, health questionnaire, Hypoglycemia Patient Questionnaire [2] Health Literacy Screener (Newest Vital Sign) [55]	Week 0
Aim 1		
Recruitment	Number recruited, screened, eligible, consented	Weekly
Retention	Attendance rate; completion rate	Weekly
Acceptability	Participant evaluation survey and interview (Appendix P4)	Week 8
	Advisory panel	End of study
Aim 2		
FOH	Hypoglycemia Fear Scale-II (HFS-II [52])	Weeks 0, 4, 8,12
Glycemic measures		
Glycemic control	A1C (A1C Now®)	Weeks 0, 8, 12
Glycemic variability	RT-CGM (Dexcom®): daily glucose standard deviation (GlucSD), continuous net glycemic action (CONGA), coefficient of variation (CV%), interquartile range (IQR), time spent in hypo- and hyperglycemia and time in range	Weeks 0–8
Diabetes self-management	Diabetes Self-Management Questionnaire [54]	Weeks 0, 8, 12

#### Glycemic variability

Subcutaneous interstitial glucose levels will be monitored using Dexcom G-series continuous glucose monitoring systems® (San Diego, CA). To analyze GV, the frequency and time spent in hypo- and hyperglycemia and time in range will be calculated (percentage and minutes; < 70 and > 180 mg/dL). GV will be determined by calculating the daily glucose standard deviation (GlucSD), continuous net glycemic action (CONGA), coefficient of variation (CV), and interquartile range (IQR) [57, 58].

#### Related variables

Self-efficacy, anxiety, diabetes distress, depressive mood, and quality of life will be measured with validated instruments (Self-Efficacy for Diabetes Scale [59], General Anxiety Disorder-7 Item [GAD-7] [60], Diabetes Distress Scale [61], Center for Epidemiological Studies Depression Scale [CES-D] [62], and Ferrans and Powers Quality of Life Index-Diabetes [55], respectively, at weeks 0, 8, and 12).

### Data safety monitoring

A data safety monitoring committee (DSMC) will be formed to evaluate accumulated data for participation safety, study conduct, and progress. The DSMC will be comprised of an interdisciplinary team of professors from the University of Illinois at Chicago and will be independent of the study sponsor. The DSMC will submit an annual report to the study team, University Institutional Review Board, and the study sponsor.

### Statistical analysis

The statistical estimation method for this study is a mixed-effects model with repeated measures (SPSS).

Aim 1: Feasibility will be evaluated by assessing recruitment, retention, and participant evaluation. Records will be kept of the number of recruited, screened, eligible, and consented subjects. Retention will be evaluated by weekly attendance (percentage session attendance, program completion rates). Acceptability will be determined through participant evaluation (written evaluation and interview at program completion and a convened advisory group of previous participants). As part of feasibility, we will also track the number of RT-CGM sensor failures, placement sites, time to failure, and adverse sensor site problems.

Aim 2: We will evaluate the effects of within-group and between-group differences from baseline (week 0) to program completion (week 8) and post program (week 12) on the outcomes FOH, self-management, glycemic control, and GV, using an intent-to-treat approach. To address sex as a biologic variable, sex differences in primary and secondary outcomes will be explored. Diabetes duration and depressive mood will also be statistically controlled.

Hypothesis 1: FOH will be reduced. Within-group and between-group differences in HFS worry score from baseline to study completion and post program will be compared using a mixed-effects model.

Hypothesis 2a: Diabetes self-management will be improved. Within- and between-group differences in the Diabetes Self-Management Scale score from baseline to study completion and post-program will be compared using a mixed-effects model.

Hypothesis 2b: Glycemic control. Within- and between-group differences in A1C from baseline to study completion and post-program will be compared using a mixed-effects model.

Hypothesis 2c: GV will decrease. GV will be determined through GlucSD, CONGA, CV%, and IQR, as well as daily time spent in hypo- or hyperglycemia. Within- and between-group differences will be calculated from daily RT-CGM recordings using a mixed-effects model.

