### Sample size determination

The sample size estimate will allow examination of within-group and between-group differences from beginning to end of the intervention and to calculate effect sizes to power a future larger study. To determine the sample size to meet these goals, the mean, SD, and mean/SD of FOH levels from our pilot studies were used to estimate the expected effect size [48]. The expected estimated effect size was 0.72. Twenty-five subjects will be required in each group (treatment and control; *n* = 50 total). A 20% attrition rate is expected, based on previous psychoeducational interventions in T1D [39, 41, 43]. Thus, we will accrue 30 subjects per group, to achieve a final sample size of 25 subjects per group (*n* = 50 total).

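### The individual acceptability survey and interview are scheduled once, at week 8, with no evaluation described for participants who leave earlier, so the acceptability result may rest mainly on completers

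*Protocol article*

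**What the plan says.** All references are to the Protocol article.

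- **Aim.** The specific aims in the Background make feasibility and acceptability of FREE the two parts of Aim 1.
- **How acceptability is judged.** Statistical analysis, Aim 1, names two sources: "written evaluation and interview at program completion and a convened advisory group of previous participants". The Aim 2 paragraph of that section equates program completion with week 8.
- **When.** In Table 3 (Baseline and post-intervention measures), the acceptability row reads "Participant evaluation survey and interview", with frequency week 8. A second line, "Advisory panel", is timed at the end of the study.
- **Expected loss.** Sample size determination says "A 20% attrition rate is expected, based on previous psychoeducational interventions in T1D" and then "we will accrue 30 subjects per group, to achieve a final sample size of 25 subjects per group".
- **What is recorded on leavers.** Session attendance and program completion rates are tracked weekly, under retention.
- **Early stopping.** Study population and recruitment lists participant request and a decision by the psychologist or interventionist as grounds for discontinuing. The follow-up it mentions is a list of counseling resources. It describes no exit evaluation.

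**The concern.** A survey held once, at the end of an eight-week program, reaches those who are still there. In Table 1 the fear hierarchy is built in week 4 and exposure practice fills weeks 5 to 7. A participant who finds exposure work unacceptable could plausibly leave in those weeks, before the one scheduled individual evaluation.

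The retention data do not fill this gap. Attendance and completion show that someone left, not what that person thought of the therapy. They are also an imperfect proxy for liking it: the Participant retention strategy section describes the glucose monitor as an incentive and retention factor in previous studies, and participants are compensated at weeks 4, 8 and 12. Some may stay for reasons other than the therapy, and some may leave for reasons unrelated to it.

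The Abstract presents the pilot as the foundation for a larger trial. If acceptability is learned mainly from completers, that trial may be planned on too favourable a view of the intervention, and without the leavers' own account of why they left.

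**Working it through.** **1. How many could be missed.** The inputs, from Sample size determination, are 25 per group at the end, 20% attrition and 30 accrued per group.

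- Reproducing the plan's figure: 25 × (1 + 0.20) = 30 per group, as stated.
- Loss implied by the plan's own final count: 30 − 25 = 5, and 5/30 = 16.7%.
- Loss at a literal 20%: 30 × 0.20 = 6, leaving 24.

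So 5 to 6 of the 30 FREE participants could lack the individual evaluation. This assumes that all expected attrition falls before week 8 and that leavers are not approached. The article does not date the attrition, and follow-up runs to week 12.

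**2. Effect on an acceptability percentage.** The article gives no acceptability rate, so one must be assumed. Let p_c be the proportion of completers who find FREE acceptable, p_d the proportion of leavers, d the number of leavers, and N = 30.

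- All-randomised proportion = [p_c × (N − d) + p_d × d] / N
- Completer figure minus all-randomised figure = (d/N) × (p_c − p_d)

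**3. Illustration, with d = 6 and an assumed 22 of 24 completers.**

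- Completers only: 22/24 = 91.7%
- No leaver finds it acceptable: 22/30 = 73.3%
- Five of six leavers do: 27/30 = 90.0%
- All six do: 28/30 = 93.3%

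The completer figure could be too high by up to 91.7 − 73.3 = 18.4 points (18.3 before rounding), or too low by up to 93.3 − 91.7 = 1.6 points (1.7 before rounding).

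**4. Range over other assumed completer rates.** The largest overstatement is (d/N) × p_c, at p_d = 0. The largest understatement is (d/N) × (1 − p_c), at p_d = 1.

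| Assumed p_c | Leavers d | Largest overstatement | Largest understatement |
|---|---|---|---|
| 80% | 5 | 13.3 points | 3.3 points |
| 80% | 6 | 16.0 points | 4.0 points |
| 90% | 5 | 15.0 points | 1.7 points |
| 90% | 6 | 18.0 points | 2.0 points |
| 100% | 5 | 16.7 points | 0 |
| 100% | 6 | 20.0 points | 0 |

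If leavers and completers hold the same views, the difference is zero. When the completer rate is high, the possible error is lopsided: there is far more room for the completer figure to be too high than too low.

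**The case against.** The strongest reply is that this is a condensed article and that its silence about leavers is not a decision to exclude them. Three stronger readings are tempting, and the document supports none of them.

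- **That week 8 is the only time acceptability is assessed.** It is not. The advisory panel at the end of the study is a second source, and its description as previous participants is not limited to completers. But nothing says that non-completers will be invited, and a convened group does not replace individual evaluations.
- **That those who drop out are never asked.** The article does not say so. Week 8 is a calendar time point, Aim 2 follows an intent-to-treat approach, and someone who has stopped sessions might still be contacted then. The appendix cited for the survey is not available. Against this, the text ties the evaluation to program completion, which points towards completers.
- **That the result is biased in the favourable direction.** This is an inference. Leavers' views are unknown, the top of the range (93%) lies just above the illustrative 92%, and the bias is nil if leavers resemble completers.

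It is also fair that the article defines no acceptability percentage or denominator, so the figures here are illustrative. Aim 1 would show retention beside the evaluations, so a reader would see how many left. The section on missing data commits to studying missing-data patterns, but that cannot recover an interview that was not held.

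What does not stand is the claim that this is merely an omitted detail. Two places in the article fix the timing of the individual evaluation, and both give the same single point.

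**Conclusion.** The point holds as a weakness in a stated schedule. The individual survey and interview are set once, at week 8, no evaluation is described for those who stop earlier, and the panel is not stated to include them. Acceptability may therefore rest mainly on completers, and it is likely to look too favourable if those who leave are less satisfied.

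The size is 5 to 6 of 30 FREE participants without an individual evaluation, if all expected attrition precedes week 8. Under an assumed 22 of 24 favourable completers (92%), the all-randomised figure lies between 73% and 93%. The range depends on an acceptable-or-not rating that the article does not itself define.

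The change is worth making because it affects half of Aim 1 and what the larger trial will be built on. It does not touch the primary hypothesis or any Aim 2 analysis.

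**What to change.** In Table 3 and in the Aim 1 paragraph of Statistical analysis:

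1. Give the same evaluation survey, with a brief exit interview where the participant agrees, at week 8 or at discontinuation of sessions, whichever comes first.
2. Report acceptability with the number randomised to FREE as denominator, stating how many responded, plus a bound that counts non-responders as not acceptable.
3. State that non-completers will be invited to the end-of-study advisory panel.

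The cost is small. The survey and interview already exist, and only the timing rule and the reporting sentence change. Some leavers will not respond, and the reported figure may be less favourable. Partial response still helps: with 30 randomised, the width of the range is the number of non-responders divided by 30. It starts at 6/30 = 20 points, and each leaver who replies narrows it by 1/30 = 3.3 points.

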### Randomization and masking

Randomization will be computer-generated (using REDCap) with permuted blocks in multiples of two and stratified by gender. The randomization process will be overseen by the study statistician (CP). The treatment allocation will be concealed until the time of randomization. Due to the nature of the intervention, participants and their respective interventionists will be aware of their treatment allocation. The project manager will also be aware of the treatment allocation; all other study staff will be masked. Study participants will enter questionnaire data for the primary study outcome directly into REDCap. Secondary outcomes are objectively measured, and those who will analyze these outcomes will be masked to treatment allocation until study completion. At the baseline visit, the project manager and study participant will be informed of the treatment allocation through REDCap. The project manager will then coordinate the first intervention visit with the appropriate interventionist. If an adverse event occurs, unmasking would be permissible.

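### The stated covariates for the mixed-effects model leave out the gender stratum and week-0 worry, which may cost precision that data already collected could recover

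*Protocol article*

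**What the plan says.** **Randomisation.** The section on randomization and masking specifies "permuted blocks in multiples of two and stratified by gender".

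**Analysis.** The statistical analysis section names a repeated-measures mixed-effects model as the estimation method. Under Aim 2 it says that "sex differences in primary and secondary outcomes will be explored", and the next sentence reads "Diabetes duration and depressive mood will also be statistically controlled". For Hypothesis 1 the text is "Within-group and between-group differences in HFS worry score from baseline to study completion and post program will be compared using a mixed-effects model".

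Gender is not named as a term in the model. Week-0 worry is not named as a covariate, and nothing says whether the two arms share a baseline mean.

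**Visits.** Table 3 lists the Hypoglycemia Fear Scale-II at weeks 0, 4, 8 and 12, and self-management and A1C at weeks 0, 8 and 12. RT-CGM variability runs over weeks 0–8. CES-D is measured at weeks 0, 8 and 12.

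**Sample size.** "The expected estimated effect size was 0.72"; "Twenty-five subjects will be required in each group"; "A 20% attrition rate is expected". Accrual is set at 30 per group.

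**The concern.** The article picks two adjustment variables by name, but neither is the factor that the randomisation balances on, nor the outcome's own baseline value, which is usually its strongest predictor.

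The treatment estimate stays valid without them. The cost is precision. If gender predicts the outcome contrast, a model without it has a standard error that is larger than it need be. If each arm keeps its own baseline mean, chance imbalance in week-0 worry feeds directly into the estimated difference. At about 25 evaluable participants per arm, in a pilot whose effect sizes are meant to power a larger trial, that imprecision also carries forward.

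**Working it through.** **1. Inputs.** From the article: effect size 0.72, 25 per group, 30 accrued, 20% attrition. Not stated, so assumed: alpha 0.05, power 80%, correlation r between week-0 and week-8 worry from 0.3 to 0.8, equal variance at both visits. The article does not say whether 0.72 refers to the week-8 score or to the change.

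**2. The plan's own figure.** A one-sided 5% t-test with 80% power needs 24.6, so 25 per group, which matches. A two-sided 5% t-test needs 31.3, so 32. With 25 per group, two-sided power is 70% (t-test) or 72% (normal approximation). Thirty per group less 20% leaves 30 × 0.8 = 24.

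**3. Baseline adjustment against change.** In units of the score variance, the change has variance 2(1−r) and the baseline-adjusted score has 1−r². The ratio is (1−r²)/[2(1−r)] = (1+r)/2.

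| r (assumed) | Variance ratio | Fall in SE | Power at 25 per arm if 0.72 is on the change scale (two-sided 5%, normal; 72% unadjusted) |
|---|---|---|---|
| 0.3 | 0.65 | 19% | 88% |
| 0.4 | 0.70 | 16% | 86% |
| 0.5 | 0.75 | 13% | 84% |
| 0.6 | 0.80 | 11% | 81% |
| 0.7 | 0.85 | 8% | 79% |
| 0.8 | 0.90 | 5% | 77% |

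At r = 0.5, 25 adjusted participants per arm carry the information of 25/0.75 = 33 unadjusted.

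If 0.72 is instead on the week-8 SD scale, power for change against adjusted is 58% against 76% (r = 0.3), 72% against 84% (r = 0.5) and 91% against 95% (r = 0.7).

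**4. Does a mixed model avoid this?** Only with the right baseline specification. Generalised least squares with four visits, compound symmetry and 25 per arm gives this variance for the week-8 contrast:

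| r | Separate baseline means: 2·2(1−r)/25 | Common baseline mean: 2(1−r²)/25 |
|---|---|---|
| 0.3 | 0.112 | 0.0728 |
| 0.5 | 0.080 | 0.0600 |
| 0.7 | 0.048 | 0.0408 |

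The first column equals a raw change analysis and the second equals baseline adjustment. The Hypothesis 1 sentence fits both.

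**5. Gender.** If gender explains a share R² of the residual variance of the contrast, the SE falls by 1−√(1−R²). For an assumed R² of 0, 2, 5 and 10% that is 0, 1, 2.5 and 5%, and power moves from 72% to 72, 73, 74 and 77%.

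**The case against.** Four points can be made on the other side.

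- **Raw change is not specified.** A reader might infer that the primary analysis tests raw change scores. The article does not say so. It names a repeated-measures mixed model and a contrast from baseline, and never makes change the dependent variable. Under a common baseline mean the loss is zero. This stands, so the loss is conditional.
- **Week 4 is not excluded.** A reader might infer that week-4 worry is discarded because Hypothesis 1 names only completion and post-program. The sentence names the comparisons, not the visits entered in the model. This stands too.
- **Gender may be covered.** The word *also* in the sentence on diabetes duration and depressive mood follows directly on the sentence about sex, and could be read as adding to it. But exploring sex differences is not the same as adjusting for the stratum, and no sentence puts gender in the model. In a pure change contrast, moreover, a sex difference that is constant over time cancels out. An inflation figure based on a sex difference in level therefore cannot be carried over.
- **An article condenses.** Model terms may be set out in the full protocol or an analysis plan that is not shown. This lowers the weight of the point but does not remove it, because the article prints a covariate list and a contrast that do not match its own randomisation.

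**Conclusion.** The point holds in a modest form. The stated covariates omit the stratification factor, and the handling of week-0 worry is left open between two specifications that differ in precision. With separate baseline means, the SE of the week-8 contrast is larger than it need be: adjustment would lower it by about 5% (r = 0.8) to 19% (r = 0.3). With a common baseline mean already intended, there is no loss. The gender term is worth about 0–5% of the SE, depending on how prognostic gender is, and its main merit is consistency with the randomisation.

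The variance ratio needs only equal variances at the two visits. The power figures rest on more: an assumed correlation, a two-sided 5% test and an assumed scale for 0.72. They illustrate and do not show that the trial is underpowered. The validity of the treatment estimate is not in question.

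**What to change.** For the HFS worry score, state a repeated-measures mixed model with arm, visit, arm by visit, gender stratum, week-0 worry (as a covariate or through a common baseline mean), diabetes duration and week-0 CES-D. Keep week-4 worry in the model. A common mean presumes that week-0 worry is recorded before allocation is disclosed. Use the same form for self-management and A1C at their own visits.

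For the daily RT-CGM variability outcomes, adjust for gender and the run-in value, and choose a covariance structure suited to daily data. An unstructured matrix over 56 days would have 56 × 57/2 = 1,596 parameters for 50 participants, so the visit-based model should not be copied across.

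The cost is analysis wording only. Every variable is already collected, and the article reports that recruitment was still under way.

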#### Management of missing data

Missing values will be analyzed to better understand the characteristics of missing patterns. Once the missing patterns are understood, an imputation method will be determined if appropriate. As this is a pilot study, missing value information will be used to plan the next stage and larger study.

### Participant retention strategy

Both FREE intervention and attention control groups will (1) have weekly sessions scheduled at a time convenient for the participants; (2) wear a RT-CGM; (3) receive appointment reminders; (4) be compensated at weeks 4, 8, and 12; and (5) receive a personalized folder with copies of their CGM recordings at study’s end. Weekly sessions for both the FREE and attention control groups will include topics of interest and value to the study population. Use of RT-CGM technology is highly desirable for many young adults with T1D and served as both an incentive and retention factor in our previous studies [48].

